#### Study processes

Seven to 20 weeks before the invitation date, the included citizens in study arms 1 and 2 will receive a link to the baseline questionnaire via their digital mail (with remote printing for exempted citizens). Questionnaire reminders will be sent out after two weeks. Instead of a second questionnaire reminder, non-respondents will be contacted via telephone after four weeks and invited to fill out the questionnaire via telephone interview. In a pilot study, the response rates among lower educational attainment and medium/higher educational attainment citizens using an invitation and a two-week reminder were assessed at 27% and 55%, respectively. The response rates increased to 40% and 64%, respectively, in the two groups, by using telephone interviews. Accordingly, we expect telephone interviews to help reach more of the lower educational attainment citizens. Questionnaire respondents will also be asked for consent to the obtaining and analysis of screening data (date of invitation, reminder, receipt of test in laboratory, and test result) from the screening program database.

Citizens who respond to the questionnaire and give consent to the use of registry data will be randomly allocated into study arms 1 and 2. Allocation will be performed in the ratio 1:1 and will use a computer-generated algorithm for randomization, based on a simple randomization procedure. Randomization will be conducted based on the study participants’ record-ID numbers. Participants will not be able to change study arm after allocation and there will be no blinding.

Citizens who take up screening within 45 days after the screening invitation and citizens with medium or higher educational attainment (i.e. 10 years or more of education) will be excluded from the analyses after randomization. This might cause attrition bias. However, randomization will be conducted externally before screening uptake is known. Furthermore, educational attainment will not be available to researchers at an individual level, unless data are pseudonymized. However, educational level and screening uptake within 45 days of invitation is not expected to be associated with study arm and, hence, no attrition bias is expected.

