When citizens in the intervention group are due for a screening reminder, they will concurrently receive a separate mail containing a link for the decision aid. This strategy was chosen in order to avoid information overload, since other conventional information material is sent out along with the screening invitation. Further, first invitations are sent out by postal mail, and hence, the link is better provided in the reminders that are sent by digital mail.

Forty-five days after the citizens have received the intervention/screening reminder, they will receive the follow-up questionnaire. Reminder procedures for the follow-up questionnaire will be the same as for the baseline questionnaire. Citizens who do not return follow-up questionnaires within six weeks (i.e. going to the last page in the questionnaire and pressing submit) will be excluded from the study, since the consent to use data in the project will not have been given.

Citizens in the historic study arm will receive one questionnaire 6–8 months after being invited to participate in CRC screening. Reminder procedures for this questionnaire will be the same as for the previous questionnaires.

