#### Primary outcome

Informed choice will be evaluated based on the following primary outcomes: consistency of knowledge about CRC screening, attitudes towards CRC screening, and screening uptake [34].

Knowledge will be measured via questionnaire before and after intervention using a seven-item scale developed by the authors based on both a literature search and patient information needs as previously clarified in focus group interviews [25]. Post-intervention levels and changes from baseline to follow-up will be evaluated.

Screening attitudes will be estimated using the translated four-item attitudes scale, ranging from 4 to 28 points [34]. The scale has been translated into Danish from English with conventional forward-backward translation [35]. Attitudes will be assessed at baseline and at follow-up.

Data on screening uptake will be collected from the CRC screening program database. Citizens will be defined as having taken up CRC screening if they return a stool sample within three months (90 days) after the screening invitation has been sent out [36].

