### Statistical methods

All statistical analyses will be carried out in Stata/SE 14 (STATACorp LP, College Station, TX, USA). Analyses will be carried out on a 5% significance level, stratified to gender. Estimates will be presented with 95% confidence intervals. Intention-to-treat analyses will be conducted.

Pearson’s chi-square test will be used to test differences in demographic characteristics between respondents and non-respondents as well as between those included in each study arm with lower educational attainment, in order to test for baseline differences. Furthermore, differences in educational attainment and screening uptake within 45 days in each study arm will be compared in order to evaluate the risk of attrition bias.

The main outcome of the trial is informed choice. Informed choice is difficult to measure and the evaluation will be based on adequate knowledge about CRC screening and consistency between attitudes towards CRC screening and screening uptake. This will be judged at group level not individual level. [46] Differences in distributions of responses to knowledge, attitudes, uptake, decisional conflict, and worries in the study arms will be analyzed using the independent sample t-test for continuous variables and Pearson’s chi-square test for categorical variables. The relative risk (RR) will be estimated for uptake using a logistic regression analysis with study arm 2 as the reference comparing to both study arm 1 and the historic cohort. Citizens are defined as having taken up CRC screening if they returned a stool sample within three months after the screening invitation was sent out [47]. For the numeric scale outcomes, a linear regression analysis will be conducted to compare the means between study arms 1 and 2 and study arm 2 and the historic cohort, using study arm 2 as the reference. For ordinal scales, not normally distributed as assessed by histograms and qq-plots, ordinal regression analyses will be conducted, estimating odds ratios for higher scores in study arm 1 and the historic cohort as compared to study arm 2, using study arm 2 as the reference.

Further, generalized linear models from the binary family will be conducted to test if socioeconomic variables (including health literacy) modify the effectiveness of the decision aid on knowledge, attitudes, and uptake. *P* values for these analyses will be estimated using the Wald test.

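### Registry-based uptake is to be compared only among follow-up responders, despite registry consent taken before randomization; the consent statements conflict and the uptake analysis is not intention-to-treat as written

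*Protocol article*

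**What the plan says.** Under Study processes, baseline respondents are asked for registry consent: "Questionnaire respondents will also be asked for consent to the obtaining and analysis of screening data". The data covered are the dates of invitation, reminder and laboratory receipt, and the test result. This consent is a condition of allocation: "Citizens who respond to the questionnaire and give consent to the use of registry data will be randomly allocated into study arms 1 and 2".

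The same section sets the follow-up rule. "Forty-five days after the citizens have received the intervention/screening reminder, they will receive the follow-up questionnaire". Those who have not submitted it within six weeks "will be excluded from the study, since the consent to use data in the project will not have been given". No exception is made for outcomes that do not come from the questionnaire, and Power calculations equates follow-up responders with the study participants.

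Uptake does not come from the questionnaire. The Primary outcome section states: "Data on screening uptake will be collected from the CRC screening program database". A citizen counts as screened "if they return a stool sample within three months (90 days) after the screening invitation has been sent out". Statistical methods describes the registry and IT systems as nearly complete, and adds: "Intention-to-treat analyses will be conducted".

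**The concern.** Every randomized citizen has already consented to the analysis of screening data, so lack of consent does not obviously explain why non-submitters lose their uptake outcome. Either the baseline consent covers uptake and the exclusion is unnecessary for it, or a second consent governs and the baseline statement says too much. The protocol does not say which.

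The consequence is statistical. Submitting the follow-up form happens after the decision aid has been sent and at or after the close of the uptake window, in a trial without blinding. Both arm and uptake could influence it. Restricting the uptake comparison to submitters conditions on that event, so the protection given by randomization is no longer assured.

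The attrition-bias argument under Study processes deals with two other exclusions: educational attainment, which is a baseline trait, and a sample returned within 45 days, which precedes the decision aid. The attrition check in Statistical methods covers the same two. Neither looks at follow-up response by arm.

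The stake is a primary element and the stated analysis principle. The Study design section frames the trial as a pragmatic evaluation of offering the aid, and for that question all eligible randomized citizens are the natural population.

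**Working it through.** **Timing.** The reminder, and in arm 1 the decision aid, goes out at day 45 after the invitation. The follow-up form goes out 45 days later: 45 + 45 = day 90. The uptake window closes at day 90. The six-week limit for submission ends at about 90 + 42 = day 132. Whether a citizen is kept is therefore settled when uptake is already determined.

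**The plan's own figure.** Power calculations gives 200 per group for a 14-point difference, 5% significance and 80% power. The base rate is not stated. With 43% versus 57% (assumed), a two-sided test and pooled variance under the null:

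n = [1.960·√(2·0.5·0.5) + 0.8416·√(0.43·0.57 + 0.57·0.43)]² / 0.14² = (1.386 + 0.589)² / 0.0196 ≈ 199, rounded up to 200.

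The figure reproduces, and 50% versus 64% gives 196. It concerns attitudes; the issue here is who enters the uptake analysis.

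**Participant flow per arm.** Inputs from Power calculations: 5000 sampled, 60% baseline response, 26% lower educational attainment, 47% without a sample by day 45, 80% follow-up response. Multiplying treats the rates as independent.

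- Eligible with registry uptake: 5000 × 0.60 × 0.26 × 0.47 = 366.6, about 367
- Left after the follow-up exclusion: 366.6 × 0.80 = 293.3, about 293
- Uptake outcomes lost: 366.6 × 0.20 = 73.3, about 73

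With the pilot's 40% baseline response in citizens with lower educational attainment (Study processes): 5000 × 0.40 × 0.26 × 0.47 = 244.4, and × 0.80 = 195.5. The share lost stays at 20%.

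**Precision.** Keeping all eligible citizens multiplies the standard error by √0.80 = 0.89. For an assumed 30% versus 40% uptake, power is about 72% with 293 per arm and 81% with 367.

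**Bias, illustrations only.** The protocol gives no response rates by arm and uptake. All rates below are assumed, with no true effect.

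*A. Unequal overall response.* True uptake is 35% in both arms and 90% of screened citizens respond. A fraction r of unscreened citizens responds. Observed uptake = 0.35·0.90 / (0.35·0.90 + 0.65·r).

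| Arm | r | Overall response | Observed uptake | Ratio to control |
|---|---|---|---|---|
| Control | 0.75 | 80.3% | 39.3% | – |
| Intervention | 0.70 | 77.0% | 40.9% | 1.04 |
| Intervention | 0.65 | 73.8% | 42.7% | 1.09 |

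*B. Equal overall response of 80%.* Among screened citizens, 90% respond in the intervention arm and 80% in the control arm. Observed uptake = true uptake × response of the screened / 0.80.

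| True uptake | Intervention | Control | Difference | Chance of a significant result favouring the aid, 293 per arm |
|---|---|---|---|---|
| 20% | 22.5% | 20% | 2.5 points | about 11% |
| 30% | 33.8% | 30% | 3.8 points | about 16% |
| 40% | 45% | 40% | 5.0 points | about 23% |

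The ratio is 0.90/0.80 = 1.125 in each row, and the nominal chance in that direction is 2.5%. Similar overall response in the two arms is therefore not sufficient reassurance.

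*C. Same dependence in both arms.* If 90% of screened citizens respond in both arms with 80% overall, true uptake of 30% is observed as 33.8% in both. The level shifts, but the comparison under no effect is unbiased.

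**The case against.** **Consent scope.** The follow-up rule may refer to a separate, broader project consent given by submitting the form. The baseline consent lists screening-program data only, while identifying lower educational attainment needs linkage to Statistics Denmark. The consent pages and questionnaires are not at hand. This stands: it cannot be assumed that a change of wording suffices. It does not remove the conflict, because the text still leaves open which consent governs registry uptake.

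**Existing checks.** Statistical methods also compares demographics of respondents and non-respondents, and of citizens with lower educational attainment included in each arm. This is a partial safeguard. It does not compare follow-up response by arm, and balance on demographics among responders cannot rule out response that depends on arm and uptake together.

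**One common population.** Informed choice is judged at group level from knowledge, attitudes and uptake, so using the same citizens for all three is defensible for that judgement. It does not justify the same restriction for the relative risk of uptake.

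**Historic cohort.** Its members enter only by answering a questionnaire sent after uptake. Removing the restriction from the randomized arms alone would make that comparison less like-for-like. This stands and shapes the fix.

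**A stronger reading.** A reader might infer that the uptake result will be biased, or biased in favour of the decision aid. The protocol does not support that. Illustration C gives no bias in the null comparison, and illustrations A and B rest on assumed rates that could equally be reversed.

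**Conclusion.** The point holds as a conflict between stated rules. Consent to analyse screening data precedes randomization, but non-submission of the follow-up form removes a citizen from the whole study on grounds of consent. As written, uptake in arms 1 and 2 is compared in about 80% of eligible randomized citizens: 293 of 367 per arm on the planned rates, 196 of 244 at the pilot's baseline response. The 20% loss rests only on the planned follow-up response; the counts also assume that the stated rates multiply.

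That comparison is not intention-to-treat, and it is open to selection bias if response depends on both arm and uptake. Nothing in the protocol fixes the size or direction. Nor does it show that baseline consent is enough for the remedy; that must be established first.

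**What to change.** 1. Reconcile the two consent statements under Study processes: say which consent governs screening data and whether it extends to the education linkage.
2. If the baseline consent suffices, compare uptake between arms 1 and 2 in all randomized citizens with lower educational attainment and no sample by day 45, whether or not they submit the follow-up form. Confine the follow-up exclusion to knowledge, attitudes, worry and decisional conflict.
3. Add follow-up response by arm to the attrition check in Statistical methods.
4. Keep a responder-only uptake analysis for the comparison with the historic cohort, and as a sensitivity analysis for arms 1 and 2.
5. If the consent actually given does not allow step 2, stop describing the uptake analysis as intention-to-treat and state the risk of selection bias.

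**Cost.** If baseline consent covers the data, the change is to protocol and analysis text plus one extra table; the extract from the screening system is already planned for the end of follow-up. If it does not, step 2 would need a change to the consent process, possibly with approval. Step 5 is then the fallback and costs only wording.

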**Methods:**

The LEAD (Lower Educational Attainment Decision aid) trial will be conducted as a two-arm randomized controlled trial among 10,000 50–74-year-old citizens, resident in the Central Denmark Region not yet invited to take up colorectal cancer screening. Citizens will receive a baseline questionnaire. Respondents will be allocated into the intervention or the control groups. Citizens in the intervention group will receive the decision aid whereas the control group will not. Those who return a stool sample within 45 days after receiving the screening invitation and those with medium or higher educational attainment are excluded. Both groups will receive a follow-up questionnaire 90 days after being invited to colorectal cancer screening.

A historic cohort consisting of 5000 50–74-year-old citizens resident in the Central Denmark Region, having received their screening invitation in the beginning of 2017 will be included. This cohort will receive a follow-up questionnaire 6–9 months after they received the screening invitation.

Informed choice will be evaluated by assessing levels of knowledge, attitudes, and screening uptake. Analyses will be conducted as intention-to-treat analyses. Additionally, differences between levels of worry and decisional conflict between groups will be assessed as secondary outcomes.

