## Methods

### Setting

CRC screening with biennial FIT was introduced in Denmark in 2014 with an initial “prevalence round” of invitations for four years, where all citizens aged 50–74 years are invited once, according to month of birth. Citizens turning 50 or 75 years during the prevalence round are invited just before their birthday if not invited earlier. From 2018, all citizens in the target group will receive biennial invitations (identifying incident CRC). The screening program is locally administered in five regions. This study is carried out in the Central Denmark Region, which is the second largest region with roughly 395,000 citizens aged 50–74 years [27].

In the CRC screening program, the mailed screening invitation contains a screening kit (collection tube and collection paper), instructions on how to obtain the sample, an official information leaflet, and a pre-stamped, pre-addressed envelope. If a screening sample is not returned within 45 days, a digital reminder is sent (see below). Test results are digitally mailed to the citizens within one week after the test is received at the laboratory. Citizens with a negative test result are referred to the next screening round (two-year interval) and citizens with a positive test result receive an appointment for colonoscopy. Non-participating citizens are automatically referred to the next screening round.

Danish residents are obliged to order a digital signature which is used to log in to a secure national e-mail platform, where all mandatory digital communication with Danish authorities (including hospitals) takes place via the unique civil registration number. Some citizens (8.7% of the population aged 45–74 years during the summer of 2017 [28]) can be exempted from digital communication [29] and receive conventional mail via a remote printing system, in which an external supplier prints out and sends all letters to exempted citizens.

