**Fig. 1 Fig1:**
[figure not shown]
Participant *flow chart*. Figure depicting the data collection, interventions, and participant flow in the trial

The intervention and control groups receive the baseline questionnaire before the screening invitation. This might increase screening awareness and possibly screening uptake and knowledge in these groups – a true Hawthorne effect. To be able to assess the effect of the questionnaire, a historic cohort will be introduced as in other decision aid trials [30]. This group will receive their questionnaire after screening invitation and uptake assessment.

This study entails evaluating the offer to use the decision aid. Even though participants may not necessarily use it, not using the decision aid is not a specific issue in this study as it is a pragmatic evaluation of offering it in a routine screening program.

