### Outcomes

The outcomes assessed in this trial are presented in Table 1.

**Table 1 Tab1:** Trial outcomes

Outcome	Characteristics	Assessment time	Comparisons^a^	Null Hypothesis^a^
Primary outcome (Informed choice elements)				
Knowledge	Numeric scale	Baseline	1 vs. 2	No difference
	Numeric scale	Dif_Follow-up-baseline_^b^	1 vs. 2	1 > 2
	Numeric scale	Follow-up	1 vs. 2 vs H	1 > 2 and 1 > H
Attitudes	Numeric scale	Baseline	1 vs. 2	No difference
	Numeric scale	Dif_Follow-up-baseline_^b^	1 vs. 2	No difference
Uptake	Dichotomous	Follow-up	1 vs. 2 vs H	1 > 2 and 1 > H
Secondary outcomes				
Decisional conflict	Numeric scale	Follow-up	1 vs. 2 vs H	1 < 2 and 1 < H
Worry	Numeric scale	Baseline	1 vs. 2 vs H	No difference
	Numeric scale	Dif_Follow-up-Baseline_^b^	1 vs 2	1 < 2
Effect modifiers and confounders				
Health literacy	Numeric scale	Baseline	1 vs. 2 vs. H	No difference
Background data				
Family income	Categorical	Post survey	1 vs. 2 vs. H	No difference
Occupation	Categorical	Post survey	1 vs. 2 vs. H	No difference
Marital status	Dichotomous	Post survey	1 vs. 2 vs. H	No difference
Ethnicity	Categorical	Post survey	1 vs. 2 vs. H	No difference

*H* historic study arm

^a^Group 1 refers to the intervention group and group 2 refers to the control group

^b^Dif_Follow-up-Baseline_: The mean increase or decrease in knowledge, attitude, and worry-score from baseline to follow-up will be estimated. Means will be compared between the two study arms

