#### Secondary outcomes

The 16-item decisional conflict scale [37] will be used to measure decisional conflict, i.e. uncertainty about making the right choice. It comprises five subscales, including the decisional support subscale and the (perceived) effectiveness of the decision subscale. Scores range from 0 to 100 and data are collected at follow-up.

Worry about CRC will be assessed using three items on worry about CRC. Two items assess worry and anxiety when considering CRC screening and one assesses worry about the result of a screening test. Items have also been developed by the authors based on literature searches [19, 20, 38–40]. Scores are in the range of 3–15. Assessments are made at baseline and follow-up.

Health literacy is a multidimensional measure of a person’s ability to access, understand, appraise, and apply information about healthcare, disease prevention, and health promotion [41]. It will be measured at baseline using the 16-item HLS-EU-Q16 scale [41].

The use of the decision aid will be measured among citizens receiving an invitation to use it. However, detailed process data will not be collected, since the primary aim of this trial is to investigate the effectiveness of having the decision aid provided, regardless of actually reading it. Usability and acceptability have been further assessed in the development phase of the decision aid [26].

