#### Questionnaires

Three different questionnaires will be administered in this trial: the baseline (knowledge, seven items; attitudes, four items [34]; worry, three items; health literacy – HLS-EU-Q16, 16 items [41, 44]) and follow-up (knowledge; attitudes; worry; decisional conflict, 16 items [37]) questionnaires, and the questionnaire for the historic study arm participants (knowledge; attitudes; worry; health literacy; decisional conflict) (Fig. 2).

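### Table 1 compares baseline worry across arms 1, 2 and the historic cohort, but that cohort's only worry score is taken months after its screening invitation

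*Protocol article*

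**What the plan says.** Table 1 (Outcomes) has two rows for worry. The first reads "Worry Numeric scale Baseline 1 vs. 2 vs H No difference". The second is the change from baseline to follow-up, for arm 1 against arm 2 only. No row gives worry at follow-up with the historic cohort included.

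The measurement schedule is set out elsewhere in the article:

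- **Arms 1 and 2, baseline**: "Seven to 20 weeks before the invitation date, the included citizens in study arms 1 and 2 will receive a link to the baseline questionnaire" (Study processes).
- **Arms 1 and 2, follow-up** (Abstract; Study processes): 90 days after the invitation, that is, 45 days after the reminder.
- **Worry in general** (Secondary outcomes): "Assessments are made at baseline and follow-up".
- **Historic cohort, number and timing** (Study processes): "Citizens in the historic study arm will receive one questionnaire 6–8 months after being invited to participate in CRC screening". The Abstract gives a different window and itself calls this a follow-up questionnaire: "This cohort will receive a follow-up questionnaire 6–9 months after they received the screening invitation".
- **Historic cohort, order of events** (Study design): "This group will receive their questionnaire after screening invitation and uptake assessment".
- **Historic cohort, content** (Questionnaires): "the questionnaire for the historic study arm participants (knowledge; attitudes; worry; health literacy; decisional conflict"). Each member therefore gives exactly one worry score.

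The Statistical methods section names worry among the outcomes. For numeric scales it plans linear regression of arm 1 against arm 2, and of the historic cohort against arm 2, with arm 2 as the reference. It does not say at which assessment.

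**The concern.** Worry depends on where a person stands in the screening process. Two of the three items ask about worry and anxiety when considering screening, and the third about worry over a test result. In arms 1 and 2 the baseline answers come before any invitation. In the historic cohort they come after the invitation, after the decision and, for those who took part, usually after the result: "Test results are digitally mailed to the citizens within one week after the test is received at the laboratory".

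A contrast between the two mixes differences between cohorts with differences in timing and screening experience. If the groups look alike, that does not show that the cohorts are comparable. If they differ, that does not show that they are not.

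The row also cannot serve the purpose for which the historic cohort was added, which is to gauge the effect of having received a questionnaire before the invitation. Arm 2's baseline score is collected by that very questionnaire, so it cannot contain any later effect of having completed it. For worry, that purpose needs arm 2 at follow-up against the historic cohort.

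**Working it through.** The plan states no figure to reproduce. The check compares Table 1 with the schedule; the only arithmetic is the distance between assessments.

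**Time scale.** Weeks relative to the screening invitation, with one month = 365.25 / 12 / 7 = 4.35 weeks. Times are nominal dispatch times; reminders and telephone contact spread the actual answers further.

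| Assessment | Stated in the article | Weeks from invitation |
|---|---|---|
| Arms 1 and 2, baseline | 7–20 weeks before | −20 to −7 |
| Arms 1 and 2, follow-up | 90 days after | 90 / 7 = +12.9 |
| Historic cohort (Study processes) | 6–8 months after | +26.1 to +34.8 |
| Historic cohort (Abstract) | 6–9 months after | +26.1 to +39.1 |

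**Gap in the row as printed (historic score minus arms' baseline).**
- Smallest: 26.1 + 7 = 33.1 weeks.
- Largest, 6–8 month window: 34.8 + 20 = 54.8 weeks.
- Largest, 6–9 month window: 39.1 + 20 = 59.1 weeks.

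The two sides always fall on opposite sides of the invitation, whichever window is used.

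**Gap if the arms' follow-up score were used.**
- Smallest: 26.1 − 12.9 = 13.2 weeks.
- Largest: 39.1 − 12.9 = about 26 weeks.

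Both scores would then be post-invitation. The gap shrinks but does not close.

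**How Table 1 treats the other outcomes.**

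| Outcome | Baseline row | Follow-up level row |
|---|---|---|
| Knowledge | 1 vs. 2 | 1 vs. 2 vs H |
| Attitudes | 1 vs. 2 | none |
| Uptake | none | 1 vs. 2 vs H |
| Decisional conflict | none | 1 vs. 2 vs H |
| Worry | 1 vs. 2 vs H | none |

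Knowledge, decisional conflict and worry in the historic cohort all come from the same single questionnaire. Table 1 treats that questionnaire as follow-up for the first two and as baseline for worry. Among the primary and secondary outcomes, worry is the only one with the historic cohort in a baseline row.

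**Reading Table 1 with the Statistical methods.** The regression of the historic cohort on arm 2 needs a time point for arm 2. The Statistical methods section gives none, and the only worry row with the historic cohort in it says baseline. Following both, an analyst would compare arm 2's pre-invitation worry with the historic cohort's post-invitation worry.

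**The case against.** The strongest defence is that this is a mislabelled cell. Health literacy carries the same baseline label with all three groups, although the historic cohort supplies it in the same post-invitation questionnaire. The table may therefore use 'Baseline' loosely for the one score that the cohort provides. That may well be how the entry arose, but it does not make the row usable. Health literacy is measured once in every group, is listed as an effect modifier or confounder, and is plausibly less affected by a screening decision. Worry is measured twice in arms 1 and 2, so the label decides which score is used.

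A second argument is that a worry contrast with the historic cohort is not essential. Attitudes has no follow-up row with that cohort either, and Study design names awareness, uptake and knowledge, not worry, as what the baseline questionnaire might change. This is fair: the cohort need not be compared on worry at all. If it is, the comparison should not use a pre-invitation score.

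A reader might also infer more than the document supports:

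- *That no comparison of post-invitation worry in arm 2 with the historic cohort is planned.* The Statistical methods section plans an arm 2 versus historic cohort regression for numeric outcomes. What is missing is the time point.
- *That the whole historic cohort answers with a test result in hand.* Only those who took up screening have one. The article does not state whether the exclusion of people who return a sample within 45 days also applies to this cohort, so that share cannot be derived.
- *That the row produces a false difference of a known size.* The article gives no spread for the worry score and no effect of a result on it.
- *That the row would trigger a wrong decision about the cohort.* No adjustment, exclusion or decision is tied to it.

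**Conclusion.** The point holds. The baseline worry row with the historic cohort contradicts the article's own schedule: that cohort has a single worry score, taken after invitation and uptake assessment, while the other side of the row is taken before invitation. The distance is about 33 to 55 weeks, or up to 59 with the Abstract's window, and the conclusion is the same under either. As printed, the row is informative neither about comparability of the cohorts nor about the effect of the baseline questionnaire.

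The consequence is limited. It concerns one non-randomised contrast on a secondary outcome. The randomised comparison of change in worry between arms 1 and 2, the primary outcomes and the sample size are untouched. No size in score points can be given from the document. The conclusion assumes that the two figures not shown give the historic cohort no pre-invitation assessment; nothing in the text or captions suggests that they do.

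**What to change.** In Table 1:

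1. Change the baseline worry row to 1 vs. 2, and drop the 'No difference' entry as it applies to the historic cohort at baseline.
2. Add a row for worry at follow-up, 1 vs. 2 vs H, matching the layout for knowledge and decisional conflict. State that arm 2 against the historic cohort is the contrast for the questionnaire effect, to be estimated by the regression already described in the Statistical methods.
3. Note beside the new row that a timing gap remains (about 3 months against 6–9 months after invitation), as it does for knowledge and decisional conflict, so the contrast is to be read with that caution.

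The 6–8 and 6–9 month windows should be reconciled at the same time.

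The cost is a change of wording in one table. All the scores are already collected, and neither the questionnaires nor the sample size changes.
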